### Interventions

#### Intervention development

Focus groups were held with key stakeholders comprising people at risk or living with IAD (n=3) with their informal carers (n=2) and care staff (=15) in April 2021. The aim was to understand the challenges affecting the prevention and treatment of IAD and identify useful content for a care guide and best practice for implementation. Thematic analysis of the qualitative data conducted by the researchers and the PPI panel resulted in five themes illustrating uncertainty about identifying IAD; a lack of resources and evidence-based treatments; the need to improve care; the importance of good leadership to support good care and the psychological impact of IAD. The same stakeholders who participated in the focus groups provided detailed feedback on draft versions of the IAD manual via email until consensus was reached over three face-to-face workshops between March 2021 and October 2022. Changes were made to the content based on this feedback including the use of lay terms such as pee and poo and not medical terminology (eg, urine and faeces). Workshop attendees also advocated for a guide that was simple, online and interactive. They also called for posters and flyers of the online content to be available in care homes and people’s homes to enable care staff, people living with IAD and informal carers to access the information easily. The PPI panel also felt it was important to include content on the emotional and psychological impact of IAD. An audio recording about living with IAD was made by a member of the PPI panel and added to the IAD manual.

#### Intervention content

The IAD manual is an online, interactive, educational tool with asynchronous written, audio and pictorial content. The intervention includes an illustrated flowchart with six interconnected boxes; clicking on each box reveals evidence-based content about experiences of and preventing and managing IAD. A brief overview of the content of each box and corresponding learning objectives are shown in table 1. There is also a survey at the end of the IAD manual with questions based on the content of and experience of using the IAD manual. Care staff will be emailed a certificate on completion of the questions indicating which ones they answered correctly and incorrectly. They can repeat the self-test questions if they want to improve their score. Researchers will conduct a training need analysis of care staff to identify the starting point of staff knowledge about IAD. Ten care staff at each site will be trained on preventing and treating IAD following the guidelines in the IAD manual. These staff will act as the IAD champions at each site who will be asked to subsequently support their colleagues through the e-learning. The training will be face to face or online and will take up to 4 hours per member of staff. Completion of the manual will go towards staff’s continuing professional development. A training log will be used record staff attendance, number of sessions and duration of each training session by study site.

**Table 1 T1:** Content of the intervention

Box titles	Learning outcomes
1. Improving knowledge about IAD	Describe what incontinence-associated dermatitis (IAD) is and who is most at risk Explain some of the common causes of incontinence of pee and/or poo Describe how incontinence of pee and/or poo affects people and their families
2. Assessment and management of incontinence and promoting continence	Describe what should happen when a person with incontinence of pee or poo is assessed by a nurse Explain how to take samples of pee or poo if asked Explain how to support a person to follow a toileting programme Explain what to do and what not to do when using incontinence pads
3. Steps to prevent skin damage	Describe which skin cleansers to use and which not to use Describe which products can be left on the skin to protect against IAD
4. Identifying IAD	Describe what changes are seen in the skin when IAD develops Explain how to assess the skin when cleansing or changing continence products.
5. Seeking treatment advice	Understand that skin may be damaged by other causes Know when to ask for advice and who to ask
6. Managing IAD	Describe how to treat skin which has damage caused by pee and/or poo (IAD) Explain the key steps to prevent the damage from getting worse and help skin to heal. Know when to seek help

#### Control sites

Care will remain the same during the trial for those care homes or home care agencies that have been allocated to provide usual care to prevent or treat IAD for the recruited residents and those living at home. They will have no additional training and no access to the IAD Manual.

### Recruitment

Our PPI panel and research team networks will advise on cluster sites to invite into the study. Forty-eight people with urinary and/or faecal incontinence (with or without IAD) will be recruited per study site to take part in the feasibility RCT. Researchers will liaise with care staff managers at each study site and ask them to identify potential participants they know are incontinent. If someone is not capable of deciding if they want to take part, a personal consultee will be sought (ie, nominated next of kin or whoever is nominated as the first point of contact in the person’s records). If it is not possible to either identify or contact that person within 2 weeks, then a nominated consultee independent of the project such as the person’s GP or nominated care manager will be approached. If no response from the nominated consultee is received after 2 weeks, then the person will not be included in the study. If a personal consultee is identified after a nominated consultee has signed a declaration, then the participant will be reconsented under the personal consultee process.

### Sample size

Two care agencies and four large care homes each with approximately 100 residential and nursing care beds will be recruited and randomised as a cluster (one home care agency and two care homes in region A, with equivalents in region B). An IAD prevalence of 30% would provide 180 people with IAD (from 600) and would be sufficient to estimate recruitment and retention rates (80% recruitment, n=144) with a maximum margin of error of approximately ±7%. Forty-eight individual participants with incontinence (with or without IAD) will be recruited per site, anticipating a mean of 58 people with incontinence per 100 beds, and 30 with IAD per 100 beds.^7 12^ An overview of the planned participant flow is shown in figure 2.

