## Introduction

### Background

 Incontinence‐associated dermatitis (IAD) is an irritant contact dermatitis caused by prolonged and repeated exposure of the skin to urine, faeces, or both.^1^ It is characterised by erythema, maceration and in some cases skin loss, swelling and bullae.^2^ IAD can be painful and is often associated with itch. If not prevented or treated, IAD can lead to secondary infections, increased risk of pressure ulcer development and morbidity.^3^ This can impact quality of life, such as reduced social activities and a greater dependence on formal and informal carers.

Prevalence and incidence estimates for IAD among people receiving long-term care are few and variable with no reliable UK estimates available. In a long-term care facility in the USA, IAD prevalence of 23% on admission with 8% incidence (in those without IAD at admission) was reported over 12 weeks.^4^ IAD prevalence among those with incontinence could well be higher in the community (41%)^5^ although the proportion of people experiencing incontinence is lower (~35%)^6^ than in nursing care homes (43%–77%—mean 58%).^7^ This may be due to different skincare routines or lack of support with personal hygiene at the time it is needed in the community. Among community-dwelling adults with faecal incontinence, a prevalence of IAD of 51% has been reported.^8^ Recent studies in nursing care homes in Germany estimate the point prevalence of IAD at 20.1%^9^ and IAD incidence of 23%–26% within 6 months.^10^ In the USA, the incidence of IAD was found to be 5.5% over 14 days, among nursing home residents^11^ and as high as 30% over 1 month in Belgian nursing homes.^12^

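### The 30% IAD prevalence behind the 180 expected cases is reported in the Background as a one-month incidence and is also applied to home care clients, so the 180, the 144 and the ±7% need restating

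*Protocol article*

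**What the plan says.** All places are in the protocol article.

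- Sample size takes six sites: "Two care agencies and four large care homes each with approximately 100 residential and nursing care beds". It then states that "An IAD prevalence of 30% would provide 180 people with IAD (from 600", and that this is enough to estimate recruitment and retention: "80% recruitment, n=144) with a maximum margin of error of approximately ±7" per cent.
- The same section gives the per-bed assumption, "anticipating a mean of 58 people with incontinence per 100 beds, and 30 with IAD per 100 beds", and cites references 7 and 12 for it.
- The Background attaches reference 7 to the mean of 58% incontinent in nursing care homes. That leaves reference 12 as the source of the 30.
- The Background cites reference 12 in a sentence about incidence, where the figure is "as high as 30% over 1 month in Belgian nursing homes".
- For prevalence in care settings, the Background says German nursing home studies "estimate the point prevalence of IAD at 20.1" per cent, and gives 23% on admission to a US long-term care facility.
- For people outside care homes it says that "IAD prevalence among those with incontinence could well be higher in the community (41" per cent, with about 35% of people incontinent.
- Recruitment and Eligibility criteria admit people with incontinence whether or not they have IAD.

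**The concern.** Two things do not fit together.

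First, the type of measure. New cases arising over a month are not the cases present at baseline, and only the latter give an expected number with IAD at recruitment. The Background gives no 30% prevalence for any setting. The 30% is also the highest incidence it lists; the others are 5.5% over 14 days, 8% over 12 weeks and 23% to 26% within 6 months.

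Second, the population. The base of 600 includes two home care agencies, so a nursing home figure is carried over to about 200 people living at home. For the community, the Background gives different figures.

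The 180, the 144 and the ±7% are the only statement of precision in the section, and all three start from the 30%. The expected split between people who already have IAD and people still at risk of it also depends on this input. Incidence is a secondary objective, and both prevalence and incidence are meant to inform the size of the definitive trial.

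**Working it through.** **Inputs.** From Sample size: six sites of about 100 people (four homes, two agencies), 30% with IAD, 80% recruitment, 58 incontinent per 100 beds. From the Background: 20.1% and 23% prevalence in care settings; about 35% incontinent and 41% IAD among the incontinent in the community. The agencies are taken at 100 clients each, as the base of 600 implies.

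**Formulas.** Cases = sum over settings of people × prevalence. Margin = 1.96 × √(p(1 − p)/n), with no allowance for clustering.

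**The plan's own figures.** 600 × 0.30 = 180, and 180 × 0.80 = 144. Both reproduce. The ±7% can be reached in two ways:

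- p = 0.5, n = 180: 1.96 × 0.5/√180 = 7.3%
- p = 0.8, n = 144: 1.96 × √(0.8 × 0.2/144) = 6.5%

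**Home care from the Background's figures.** 0.35 × 0.41 = 0.1435, or about 14 per 100. For 200 clients this is 28.7 cases, against 200 × 0.30 = 60 in the plan.

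**Care homes, four ways, each with 28.7 added for home care.**

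| Rate in homes (400 people) | Cases in homes | Total cases | Fewer than 180 | Recruited at 80% | Margin, p=0.5, on cases | Margin, p=0.8, on recruited |
|---|---|---|---|---|---|---|
| 20.1 per 100 | 80.4 | 109.1 | 39% | 87.3 | ±9.4% | ±8.4% |
| 23 per 100 | 92.0 | 120.7 | 33% | 96.6 | ±8.9% | ±8.0% |
| 41% of 58 = 23.8 per 100 | 95.1 | 123.8 | 31% | 99.1 | ±8.8% | ±7.9% |
| 30 per 100 kept | 120.0 | 148.7 | 17% | 119.0 | ±8.0% | ±7.2% |
| Plan: 30 per 100 at all sites | 120.0 (+ 60 home care) | 180 | – | 144 | ±7.3% | ±6.5% |

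**The population actually recruited.** With the 248 participants in the abstract, the margin at p = 0.5 is 1.96 × 0.5/√248 = 6.2%. With 48 at each of six sites, n = 288 and the margin is 5.8%. If eligibility is built up by setting, 4 × 58 + 2 × 35 = 302 eligible people give ±5.6% for recruitment. The 80% of them recruited (about 242) give ±6.3% for retention. All of these are before clustering.

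**The case against.** The strongest defence has four parts.

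**It is a planning assumption, stated conditionally.** The Background says that estimates are few and variable and that no reliable UK figure exists, and the trial is meant to estimate prevalence. This stands as a reason for showing a range. It does not explain why a figure reported as incidence is used as prevalence.

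**The replacement figures are not firm.** This stands. The 14 per 100 joins two community sources, neither reported for home care agency clients, and the article describes these services as among those most likely to look after people with incontinence. The Background also does not say whether 20.1%, 23% and 30% are per resident or per incontinent resident; if 20.1% is per incontinent resident, the shortfall is larger. A reader might infer that cases are overstated by at least a third. The documents do not fix that: correcting home care alone gives 17% fewer, and using 41% of 58 in homes gives 31% fewer. Nor do they show that 30% is the wrong prevalence, since reference 12 is not at hand and might report one.

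**The loss of precision is modest.** This stands. A reader might set ±10.5% (p = 0.5 with 87 recruited) against the plan's ±7%, but that is not like for like: at p = 0.5 the plan's own 144 already gives ±8.2%.

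**Recruitment and retention will be estimated on everyone with incontinence.** This also stands. It would be wrong to conclude that the trial's overall feasibility precision fails, because the margins on that larger group are within ±7% before clustering.

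Little else hangs on the figure. No significance testing is planned, and the feasibility threshold of at least 10% prevalence at three or more sites would still be met on expectation at 14 to 23 per 100.

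**Conclusion.** The point holds as an inconsistency of input and citation; it is not a multiplication error. Sample size treats 30% as a prevalence in all six sites. The Background reports its apparent source as a one-month nursing home incidence, gives lower prevalences for care settings, and has community figures that imply about half the rate for home care.

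On the document's own figures, expected IAD cases are illustratively 109 to 149 instead of 180, and 87 to 119 recruited instead of 144. Compared like for like, the margin widens from ±7.3% to between ±8.0% and ±9.4% (p = 0.5, on cases), or from ±6.5% to between ±7.2% and ±8.4% (p = 0.8, on the recruited number), before clustering.

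The range assumes that the community figures apply to agency clients, that 20.1% and 23% are per resident, and that each agency has about 100 clients. What is affected is the expected IAD case count and any estimate confined to people with IAD. Overall recruitment and retention precision is largely unaffected. The correction is worth making because it is specific and cheap.

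**What to change.** Reconcile the Background and Sample size sections in one of two ways: cite a source that reports 30% as a prevalence, stating its denominator, or replace it with prevalences by setting, shown as a range, and restate the 180, the 144 and the ±7%. If community figures are used for agency clients, say that this is an assumption.

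Preferably, rest the recruitment and retention precision on all incontinent participants, who are the people recruited (for example ±6.2% at p = 0.5 with n = 248, before clustering), and give the expected number with IAD separately as a range. The abstract's 248 and six sites of 48 (288) differ, so the number used should be settled first. State which p and which n the margin refers to.

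The cost is wording in one section and less favourable IAD case figures. This correction by itself requires no change to design, sites or data collection.

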### Objectives

The overall aim of this study is to evaluate the feasibility of implementing an IAD manual in community and social care settings.

The primary objectives are to:

Determine the number of adults who are eligible and agree to participate.Assess the recruitment procedures at study sites.Determine retention and attrition rates for intervention and control arms of the study.Assess the relevance and acceptability of the intervention, data collection methods and outcome measures.Evaluate intervention fidelity.

Secondary objectives are to:

Assess the incidence of IAD, IAD-related pain; satisfaction with care for the prevention and treatment of IAD and anxiety and depression.

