### Feasibility outcome analysis

The analysis will estimate rates and proportions relating to each of the feasibility outcomes, recruitment and attrition rate, of the study. The proportions will be produced alongside the 95% CI for that proportion and the raw count which those proportions are based on. The recruitment of participants over time will be presented in a plot (number or participants vs time). The recruitment into the trial will be summarised in a Consolidated Standards of Reporting Trials diagram.^38^

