### Prevalence and incidence

Prevalence, incidence and SD of IAD will be estimated to inform sample size calculations for a definitive RCT following the below thresholds for feasibility:

≥3 care homes/care agencies (50% of those participating) with ≥10% IAD prevalence before the intervention.Recruitment by care home or home care agency staff—70% of patients/residents are screened against inclusion/exclusion criteria.70% completion of outcome measures by care staff.

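### The single maximum margin of about ±7% fits recruitment among 180 people with IAD, not retention among the 144 recruited or the enrolled sample, and it ignores the six clusters

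*Protocol article*

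**What the plan says.** The Sample size section starts from about 600 people across six sites: "An IAD prevalence of 30% would provide 180 people with IAD (from 600". It then assumes that 80% of the 180 are recruited and says that this "would be sufficient to estimate recruitment and retention rates (80% recruitment, n=144) with a maximum margin of error of approximately ±7" per cent. One margin is given for two rates, and it is called a maximum. No ICC or design effect appears.

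The same section then plans 48 participants per site with incontinence, whether or not they have IAD, expecting 58 incontinent people and 30 with IAD per 100 beds. Eligibility criteria and Recruitment define the population in the same way. The abstract gives a total of 248.

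Three other places bear on precision:
- Objectives, third primary objective: "Determine retention and attrition rates for intervention and control arms of the study".
- Feasibility outcome analysis: "The proportions will be produced alongside the 95% CI for that proportion and the raw count which those proportions are based on".
- Prevalence and incidence: "Prevalence, incidence and SD of IAD will be estimated to inform sample size calculations for a definitive RCT". Dissemination says that this later trial will be a cluster trial.

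**The concern.** Recruitment and retention have different denominators. Recruitment is measured among those who could be approached, retention among those who joined. A worst-case margin that is right for the first is too small for the second.

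The denominators used, 180 and 144, are people with IAD, whereas the trial enrols all people with incontinence. The calculation also treats people as independent, although they come from six sites where managers identify the candidates, so recruitment may well differ from site to site.

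Estimation is the purpose of this trial, and the ±7% is the only quantitative justification for its size. If it is wrong as written, readers will misjudge how firmly the recruitment and retention rates are known when the definitive trial is planned.

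**Working it through.** **Inputs.** From Sample size: 600 people, 30% with IAD, 80% recruited, 48 per site, six sites, 58 incontinent per 100 beds. From the abstract: 248. From Feasibility outcome analysis: the 95% level. From the section on sequence allocation: 1:1 allocation, three sites per arm. ICC values are my assumption, with a range of 0.01 to 0.10.

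**Denominators.** 0.30 × 600 = 180; 0.80 × 180 = 144; 58 × 6 = 348 eligible, which carries the figure per 100 beds to all six sites, as the plan does with its 600; 48 × 6 = 288 recruited. Per arm: 288/2 = 144, or 248/2 = 124.

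**Formula.** Half-width = 1.96 × √(p(1−p)/n), largest at p = 0.5.

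**The plan's own figure.**
- n = 180, p = 0.5: 1.96 × √(0.25/180) = 7.3%. This matches "with a maximum margin of error of approximately ±7" per cent.
- n = 144, p = 0.5: 1.96 × √(0.25/144) = 8.2%.
- n = 144, p = 0.8: 1.96 × √(0.16/144) = 6.5%. This also rounds to 7%, but it is not a maximum.

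**Enrolled sample, people treated as independent, p = 0.5.**
- Recruitment, n = 348: 5.3%.
- Retention, n = 288: 5.8%; n = 248: 6.2%.
- Retention in one arm, n = 144: 8.2%; n = 124: 8.8%.

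**With clustering.** Multiply by √DE, where DE = 1 + (m − 1) × ICC and m = n/6 people per site. For n = 288, m = 48, normal quantile:

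| Assumed ICC | DE | Maximum (p = 0.5) | At p = 0.8 |
|---|---|---|---|
| 0.01 | 1.47 | ±7.0% | ±5.6% |
| 0.05 | 3.35 | ±10.6% | ±8.5% |
| 0.10 | 5.70 | ±13.8% | ±11.0% |

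For n = 248 (m = 41.3) the maxima are ±7.4%, ±10.8% and ±14.0%. For recruitment on 348 (m = 58) they are ±6.6%, ±10.3% and ±13.6%.

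One arm of 144 in three sites of 48, at ICC 0.05: 1.96 × √(0.25 × 3.35/144) = 14.9%. A t quantile on 5 degrees of freedom (2.571) would widen the overall margins further: for 288, to ±9.2% at ICC 0.01 and ±13.9% at 0.05.

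**The case against.** The strongest reply is that the two corrections pull in opposite directions. If the right base is everyone enrolled, then ±8.2% is not the overall margin of this trial, and the stated ±7% is conservative under independence. Even with clustering, 288 people at an ICC of 0.01 give ±7.0%. This stands: overall, whether ±7% is exceeded depends on the ICC, which the document does not give. It also stands that 144 people at 80% give ±6.5%, so for that subset the fault lies in calling the figure a maximum and applying it to retention.

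Some stronger readings are tempting but not supported:
- *The margin describes people the trial does not recruit.* People with IAD are eligible and make up 30 of the 58 incontinent people expected per 100 beds. They are a subset of those enrolled.
- *The true margin is ±9% to ±16%.* That range needs n = 144, p = 0.5, an assumed ICC of 0.01 to 0.05 and, at the top, a t quantile on 5 degrees of freedom. It cannot be derived from the document.
- *The reported confidence intervals will be too narrow.* The article names no interval method, and an analysis plan not shown may specify one that allows for clustering.
- *The definitive trial cannot be sized.* External ICCs are not excluded and would be needed anyway, since six clusters estimate an ICC poorly.
- *The SD of IAD is an error.* For a binary outcome the SD follows from the proportion, but Pilot outcome analysis summarises the Incontinence-Associated Dermatitis Intervention Tool by mean and SD, and the phrase may mean that score.
- *The plan promises ±7% in each arm.* It does not. However, retention by arm is a primary objective, and the only margin given does not cover it.

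**Conclusion.** The stated margin is wrong as written. As a 95% worst case it fits recruitment among 180 people with IAD (±7.3%) but not retention among 144 (±8.2%), an understatement of about 1.2 percentage points against the stated 7. This needs no outside assumption. Nor does the result by arm: even on the enrolled sample, the worst case is ±8.2% or ±8.8% before clustering.

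The lasting weakness is the missing allowance for six clusters. For 288 people, an ICC of about 0.01 already uses up the whole ±7%, and larger assumed values exceed it. These clustered figures rest on assumed ICCs, p = 0.5, equal site sizes and a normal quantile.

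Severity is moderate. Data analysis rules out significance testing, and the thresholds under Prevalence and incidence and Process evaluation (half of the sites, 70%, 70% and 75%) do not use the ±7%.

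**What to change.** In Sample size:
- Give separate margins for recruitment (about 348 eligible) and for retention (288 or 248), overall and by arm.
- Apply a design effect over a stated ICC range, for example 0.01 to 0.10, labelled as an assumption.
- State the confidence level and the value of p, and use the word maximum only where p = 0.5.
- Reconcile 248 in the abstract with 6 × 48 = 288.

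In Feasibility outcome analysis, state that the 95% intervals allow for clustering by site, for example from site-level proportions with a t quantile, or a Wilson interval on n divided by the design effect.

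As a secondary change, in Prevalence and incidence, say what the SD refers to. Name the control-arm proportion and the ICC as inputs to the definitive cluster trial, with the ICC read alongside external values.

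The cost is a less favourable stated margin and wider intervals: by √1.47 = 1.21 at ICC 0.01 and √3.35 = 1.83 at ICC 0.05 for 48 per site. No extra participants or data are needed.
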